### Sample size

2.8

The current study is powered for the first and primary research question, i.e., the main and interaction effects of the treatment components on the decrease of social anxiety symptoms. In the a priori power analysis, we assumed that the smallest clinically relevant difference would be a small effect size of Cohen's *d* = 0.2 for the main effect of an individual treatment component or interaction between components on pre-to-post change on social anxiety symptoms. Smaller effect sizes would be of little clinical interest and value. At an α level of 0.05, a statistical power (1-Beta) of 0.80, and a correlation between measurements with around 4- and 8-weeks interval of *r* = 0.50, based on our experience with clinical trials for SAD, we need a total of 384 participants (G*Power; Faul et al., 2007). Based on the finding that in 15 out of 17 studies, dropout rates (i.e., not providing assessment data at post-treatment) for ICBT for SAD were below 13% (Boettcher et al., 2013), we conservatively estimate a dropout rate of 20% for our study (*n* = 77 participants). Thus, we aim for a sample size of 464 participants, which results in 29 individuals per treatment condition.

As mentioned above, the logic behind how an experiment is powered differs between RCTs and factorial experiments. An RCT would compare the 16 conditions to each other, and power would be reflected in the per-condition sample size. If an RCT has a small per-condition sample size, such as 29 individuals per treatment condition, it does not have enough power to detect small effect sizes. By contrast, in factorial experiments, all participants receiving a specific component (e.g., cognitive restructuring, which is present in half of the conditions, i.e., in eight conditions) can be compared to participants who do not receive that component (also eight conditions, with 29 participants per condition). That yields a sample size of *n* = 232 per component (Collins, 2018). Since our study contains only components with two levels (absent vs present), the sample size to maintain the power to detect main effects and interactions is the same (Collins, 2018). For a detailed explanation of how factorial experiments maintain power to estimate main effects and interactions, see Collins (2018).

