### Study design

2.1

The study is a single-center, block randomized, balanced factorial trial with four treatment components (experimental factors), each evaluated at two levels (presence vs absence), resulting in 16 conditions (2 × 2 × 2 × 2; see Table 1). Although there are 16 experimental conditions, this study should not be considered a 16-arm RCT (Collins, 2018). The purpose of the factorial experiment is not to compare the 16 conditions to each other but to estimate the main effects of the four treatment components and interactions between the components. Each estimation of the main effects and interactions is based on all the conditions and, therefore, on all participants. For example, the main effect of the cognitive restructuring component will be estimated by comparing the mean of the experimental conditions in which the cognitive restructuring component is present (5, 6, 7, 8, 13, 14, 15, 16 in Table 1) vs the mean of the experimental conditions, in which cognitive restructuring is absent (1, 2, 3, 4, 9, 10, 11, 12 in Table 1). To calculate a two-way interaction (i.e. effect of one component depending on the level of the other factor), one has to calculate the difference between the average effect of one component at the two levels of the other component (present vs absent) and then averaging over all other factors. For a detailed explanation, see Collins (2018).

**Table 1 t0005:** Experimental conditions of the factorial design, with the presence (yes) and absence (no) of each component.

Condition	Psychoeducation	Cognitive restructuring	Attention training	Exposure
1 WL	No	No	No	No
2	No	No	No	Yes
3	No	No	Yes	No
4	No	No	Yes	Yes
5	No	Yes	No	No
6	No	Yes	No	Yes
7	No	Yes	Yes	No
8	No	Yes	Yes	Yes
9	Yes	No	No	No
10	Yes	No	No	Yes
11	Yes	No	Yes	No
12	Yes	No	Yes	Yes
13	Yes	Yes	No	No
14	Yes	Yes	No	Yes
15	Yes	Yes	Yes	No
16 full	Yes	Yes	Yes	Yes

WL = Wait-list condition. For ethical reasons, participants randomized to condition 1 will be offered treatment after eight weeks.

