## Discussion

3

Far from all individuals suffering from SAD seek and eventually find help, and far from all SAD patients respond fully to current evidence-based treatments. Low-threshold and cost-effective internet-based interventions can easily be distributed and flexibly used, representing a promising alternative to face-to-face therapy. With an optimized internet-based intervention, a broader population of people suffering from SAD can be reached at even lower costs and more effectiveness. The results of this trial are expected to improve current evidence-based treatments for SAD and increase the number of SAD patients fully responding to ICBT. If we know more about the active ingredients of CBT for SAD, we can probably identify better and briefer strategies that trigger change processes. Thus, understanding active ingredients and change mechanisms can optimize change and “build more potent, scalable, and efficient treatments” (Watkins et al., 2016, p. 2) of SAD.

We understand the use of the factorial trial as an appropriate approach to understand the differential effects of each component of SAD. Although other sophisticated approaches exist, for instance, component individual patient data meta-analysis (e.g., Furukawa et al., 2021), the component meta-analyses are based on the indirect comparisons between different trials. Thus, there is a higher likelihood that the observed differences can be attributed not to the various components but to the differences in the settings. Furthermore, the OPTIMIZE trial is planned to have a reasonably high sample size and sufficient power to detect even small changes.

Some potential limitations of this study should be addressed. The treatment dosage may vary across conditions and be lower in those conditions with fewer components. To prevent high variations in treatment dosage, the participants are encouraged by the program and by the guides to repeat the exercise. To address this potential limitation, we will control the overall treatment dosage of each participant by assessing adherence to the program. Also, there might be a spillover effect from the psychoeducation component once we briefly explain broad change principles used in established CBT treatment (i.e., cognitive restructuring, attention training and exposure). However, we do not offer any practical indication of implementing those techniques, and we do not provide any access to the exercises introduced in the relevant components.

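### The stated 384 participants do not give 80% power for a component main effect of d = 0.2; on the protocol's own inputs the power is about 50%

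*Protocol article*

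**What the plan says.** Section 2.8 (Sample size) of the protocol article gives every input to the calculation. The target is that "the smallest clinically relevant difference would be a small effect size of Cohen's *d* = 0.2". This is applied to a single component's main effect, and equally to an interaction, with change from before to after treatment as the outcome. The error rates are given as "At an α level of 0.05, a statistical power (1-Beta) of 0.80", and the section assumes "a correlation between measurements with around 4- and 8-weeks interval of *r* = 0.50". From these, citing G*Power, it states that "we need a total of 384 participants". A 20% dropout allowance (77 participants) brings the total to 464, or 29 in each of 16 conditions.

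The same section explains that each component is tested by setting the eight conditions that contain it against the eight that do not, 232 against 232. Section 2.1 (Study design) says "The purpose of the factorial experiment is not to compare the 16 conditions to each other". Section 2.9 (Statistical analyses) defines the primary outcome as change in the SPS and SIAS composite from baseline to week 8. The Discussion then says that "the OPTIMIZE trial is planned to have a reasonably high sample size and sufficient power to detect even small changes".

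**The concern.** A comparison of two equal halves at d = 0.2 is a familiar calculation, and 192 per half is far fewer than it normally needs. A correlation of 0.50 does not help an analysis of change: at that value, subtracting baseline adds as much variance as it removes.

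The trial exists to find out which components are active, and 0.2 is its own threshold for a difference worth having. If power at that threshold is nearer one half than four fifths, a non-significant main effect says little about whether the component works. A reader who trusts the stated power could take such a result as evidence that the component is inert. Section 2.8 assigns the same effect size and sample size to interactions, so they are affected equally.

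**Working it through.** **Inputs.** From section 2.8: d = 0.2, alpha = 0.05, power = 0.80, r = 0.50, N = 384 before dropout and 464 after, equal halves for each component. From section 2.9: the outcome is change from baseline to week 8. Sidedness is not stated; I take two-sided and return to one-sided below.

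**Step 1: standard deviation of change.** In units of the outcome SD, Var(change) = 2(1 − r) = 2(1 − 0.50) = 1. It therefore makes no difference whether d is standardised by the outcome SD or by the SD of change.

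**Step 2: power for the stated contrast.** For two halves of size N/2, the noncentrality is d·√(N/4). At N = 384 this is 0.2 × √96 = 1.96, which equals the two-sided critical value, so power is about 50%. With baseline adjustment the residual variance is 1 − r² = 0.75 and the noncentrality becomes 0.2 × √(96/0.75) = 2.26.

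| N | Power, change | Power, baseline-adjusted |
|---|---|---|
| 371 (464 × 0.80) | 0.49 | 0.60 |
| 384 | 0.50 | 0.62 |
| 464 (no dropout) | 0.58 | 0.70 |

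**Step 3: N for 80% power.** Solving the same formula gives 787 on change and 591 with baseline adjustment. With 20% dropout, dividing by 0.8, these become about 984 and 739.

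**Step 4: effect detectable with 80% power.** At 371, d = 2 × 2.80/√371 = 0.29 on change. Multiplying by √0.75 gives 0.25 with baseline adjustment.

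**Step 5: where 384 may come from.** A repeated-measures F test for the within-between interaction has noncentrality λ = f²·N·m/(1 − r). With f = 0.1, 16 groups, m = 4 assessments and r = 0.50:

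- N = 368: λ = 29.44, df = 45 and 1056, power 0.794
- N = 384: λ = 30.72, df = 45 and 1104, power 0.818

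So 384 is the first multiple of 16 above 0.80. This is the only standard repeated-measures set-up found that returns exactly 384 with the stated alpha, power and r and with f = 0.1 (half of d = 0.2). It is an inference, because the protocol does not name the module or its settings. If it is right, two things went wrong. The test is a 45-df omnibus comparison of all 16 conditions over all four assessments, follow-up included, which section 2.1 says is not the purpose. The effect size is also on the wrong scale: with two groups and two time points, a difference in change of 0.2 SD shifts each cell by 0.2/4 = 0.05 SD, so f = 0.05. Putting f = 0.05, m = 2 and N = 384 into the formula gives λ = 0.0025 × 384 × 2/0.5 = 3.84 = 1.96², the same noncentrality as in step 2.

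**Step 6: other readings.**

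- One-sided testing at 384 gives 0.62 on change and 0.73 adjusted.
- For 384 to give 80%, r would have to be about 0.76 on change or 0.72 adjusted, against the stated 0.50.
- A baseline-adjusted average of weeks 4 and 8 has residual variance (1 + r)/2 − r² = 0.75 − 0.25 = 0.50, giving power 0.79 at 384 and 0.78 at 371.

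**The case against.** The best defence is that 50% is the least favourable figure. Section 2.9 plans a linear mixed model that uses all available data, and how baseline enters that model may properly be left to the full plan. A baseline-adjusted form gives 62% at 384. This stands as a reason to quote both figures, but 62% is still well short of 80%.

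Averaging weeks 4 and 8 comes close to 80%. However, it is not the week-8 endpoint that the protocol names, and it requires the whole effect to be present already at week 4.

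The 20% dropout is described as conservative, since 15 of 17 earlier studies were below 13%. At 13%, about 404 participants remain (464 × 0.87), with power 0.52 on change or 0.64 adjusted. Full retention of all 464 gives at most 0.70. One-sided testing reaches about 80% only when baseline adjustment and no dropout at all are assumed with it, and none of the three is stated.

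Two further points stand in part. Larger effects are well covered: at 371, power for d = 0.3 is 0.82 on change and 0.91 adjusted, so the loss concerns effects close to 0.2. The protocol also sets no rule for discarding a non-significant component; the risk is one of interpretation, created by the power claim. Finally, the explanation of 384 in step 5 is conjecture. The section mentions intervals of about 4 and 8 weeks, which suggests three assessments, and the same 16-group set-up with three assessments needs 432. The conclusion does not depend on that explanation.

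**Conclusion.** The concern holds. For the effect, outcome and correlation that section 2.8 states, 384 participants give about 50% power, or 62% with baseline adjustment, and 80% would need 787 or 591. At the 371 expected to provide week-8 data, power is 49% or 60%, and the effect detectable with 80% power is d = 0.29 or 0.25. These figures assume two-sided testing at 0.05, r = 0.50, equal halves and 20% dropout. No alternative reading that keeps the stated correlation, the week-8 endpoint and the planned dropout reaches 80%. The point must be fixed, because the claimed power determines what a null component effect can be taken to show.

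**What to change.** Keep 464 and restate section 2.8. It should say that, with about 371 week-8 assessments, power for d = 0.2 is about 49% on change or 60% with baseline adjustment, and that the effect detectable with 80% power is d of about 0.29 or 0.25. It should say that interactions have the same limits. Remove the Discussion's claim of sufficient power for even small changes, or replace it with those detectable effects. Add a sentence that a non-significant main effect will be interpreted from its confidence interval relative to 0.2 and not as evidence of no effect.

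The cost is rewording in two sections and a less favourable stated power. Recruitment, endpoint and analysis stay as they are.

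### The dropout allowance is 20% of 384 rather than 20% of those randomised, so 464 leaves about 371 with post-treatment data, 13 short of the stated requirement

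*Protocol article*

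**What the plan says.** The calculation is in section 2.8 (Sample size) of the protocol article. For an effect of d = 0.2 and "At an α level of 0.05, a statistical power (1-Beta) of 0.80", with a correlation of 0.50 between measurements, the authors conclude that "we need a total of 384 participants".

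They then allow for dropout. They cite a review in which, for 15 of 17 studies, "dropout rates (i.e., not providing assessment data at post-treatment) for ICBT for SAD were below 13" per cent, and on that basis "we conservatively estimate a dropout rate of 20% for our study", which they print as n = 77. The paragraph ends: "Thus, we aim for a sample size of 464 participants", at 29 per condition.

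The next paragraph of the section argues power from 232 participants per component level, which is 464 / 2 with nothing taken off for dropout.

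**The concern.** A dropout rate applies to the people who enter the trial. If a fraction d of those randomised provides no post-treatment data, then N randomised leaves N(1 − d), and the N needed to keep n is n / (1 − d). Multiplying n by (1 + d) always gives too few.

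The printed 77 shows that the second route was taken, because 20% of 464 would be about 93. The plan therefore does not reach its own evaluable number at its own planning rate. A reader of section 2.8 would assume that 384 participants with eight-week data are secured at 20% dropout, and they are not. The stated 80% power is tied to that 384, so it carries the same shortfall.

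**Working it through.** **Inputs, all from section 2.8 of the protocol article**

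- Required number: n = 384
- Dropout rate: d = 0.20, defined as no post-treatment assessment
- Printed allowance: 77
- Planned total: 464 = 16 × 29
- Planned power: 0.80 at α = 0.05. The sidedness is not stated; two-sided is assumed here.

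**1. Reproducing the plan's figure**

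- 0.20 × 384 = 76.8, printed as 77
- 384 + 77 = 461
- 461 / 16 = 28.8, rounded up to 29 per condition; 16 × 29 = 464

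This matches the stated total exactly.

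**2. What 464 delivers at 20% dropout**

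- Expected without post-treatment data: 0.20 × 464 = 92.8
- Expected with post-treatment data: 0.80 × 464 = 371.2
- Shortfall: 384 − 371.2 = 12.8, about 13 people; 12.8 / 384 = 3.3%
- Per component level: 371.2 / 2 = 185.6, against 192 at the requirement of 384 and the 232 quoted in the section

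**3. What would keep 384**

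- 384 / (1 − 0.20) = 480 = 16 × 30
- Check: 480 × 0.80 = 384
- Difference from plan: 480 − 464 = 16, one more per condition

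Because 480 divides evenly by 16, rounding to equal cells does not explain the lower total.

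**4. Dropout that 464 tolerates**

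- 1 − 384 / 464 = 17.2%

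**5. Effect on power for a main effect (one degree of freedom, two-sided α = 0.05)**

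Taking 384 as giving exactly 0.80, the standardised effect at 384 is 1.960 + 0.842 = 2.802. It scales with the square root of the sample size:

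- 2.802 × √(371.2 / 384) = 2.802 × 0.983 = 2.755
- Power = Φ(2.755 − 1.960) = Φ(0.795) ≈ 0.787, a loss of 1.3 points

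The loss is much the same if the test is instead computed directly from d = 0.2:

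| Basis | Power at 384 | Power at 371.2 | Loss (points) |
|---|---|---|---|
| Calibrated to 0.80 at 384 | 0.800 | 0.787 | 1.3 |
| Comparison of change scores, r = 0.50 | 0.500 | 0.487 | 1.3 |
| Baseline-adjusted comparison, r = 0.50 | 0.619 | 0.604 | 1.5 |

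The lower two rows show that the absolute power depends on how the test is set up. Whether 384 is the right requirement is a separate question and is not used here.

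Among the repeated-measures settings tried, one returned 384: a within-between interaction with f = 0.1, r = 0.50, 16 groups and 4 measurements. The group and measurement counts are assumptions, since the article does not give them. In that setting power goes from 0.818 at 384 to 0.799 at 371, a loss of 1.9 points, but that is an omnibus test rather than a component main effect.

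**The case against.** Three points can be made in the plan's favour.

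**The rate has slack in it.** The 20% sits above a benchmark of 13% that 15 of 17 studies stayed under. At 13% dropout, 464 × 0.87 = 403.7 remain, comfortably above 384. The shortfall appears only if dropout lies above 17.2%. This stands as a limit on the practical consequence. It does not repair the calculation: 20% is the rate the authors chose to plan for, and the design should meet its target there. Two of the 17 studies are not described as below 13%, so dropout above 17.2% cannot be excluded.

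**The analysis does not discard dropouts.** Section 2.9 specifies intention-to-treat with a mixed model on all available data, and the primary measure is also taken at four weeks. A participant who misses week 8 but was seen at week 4 still contributes, so treating 371 as the effective sample is somewhat pessimistic. This stands in part. The recovery is incomplete for an eight-week endpoint, and the plan itself chose to inflate for missing post-treatment data. Having made that choice, it applied the rate to the wrong base.

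**The effect is negligible.** A loss of 1 to 2 points of power changes no design choice or test. That is fair as to size. It is a reason to correct the text rather than the recruitment target.

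Condensation into a journal article is not a defence: the requirement, the rate, the allowance and the total are all printed, and they disagree.

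**Conclusion.** The concern holds. On the plan's own figures, 464 randomised with 20% dropout gives about 371 participants with post-treatment data, 13 (3.3%) below the stated 384. The total consistent with 384 and 20% is 480; the dropout consistent with 384 and 464 is 17.2%.

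The cost in power is about 1.3 to 1.5 percentage points for a component main effect. This takes 384 as given, assumes a two-sided 5% test, and counts participants without post-treatment data as contributing nothing, which slightly overstates the loss under the planned mixed model. The error is clear and small. It merits correction because the sample size is a figure the trial relies on and the inconsistency shows from the printed numbers alone.

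**What to change.** Keep 464 and replace the dropout sentence in section 2.8 with wording such as: 464 randomised participants give about 371 with post-treatment data at 20% dropout; 384 are retained if dropout is at most 17%. Remove the n = 77, and base the power statement on 371, using the same G*Power settings that produced 384. Where the section quotes 232 per component level, add that about 186 per level are expected to have post-treatment data at 20% dropout.

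The cost is a sentence or two and a slightly less favourable power figure. Recruitment, the randomisation schedule and study procedures do not change. If the authors prefer to secure 384 at 20% dropout, the alternative is 480 randomised, 30 per condition, at the cost of 16 more participants.

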### Statistical analyses

2.9

Reporting will follow CONSORT E-Health standards (Eysenbach and Consort-Ehealth Group, 2011). The primary outcome is the change in the composite score of SPS & SIAS from baseline to eight weeks (post-treatment). The analyses are carried out on the basis of the intention-to-treat approach (ITT; i.e., using all randomized participants). Our primary interest is in testing the main effects and interactions. For that, we will use linear mixed models repeated measures analysis of variance (ANOVA). This approach uses all available data on each subject and does not require the imputation of missing values but estimates parameters about missing values. Furthermore, mixed models account for the correlation between the repeated measurements. Main effects and interactions are calculated based on aggregates across experimental conditions. The levels of the factors will be represented numerically by −1 (absence of a component in a condition) and +1 (presence of a component in a condition), as recommended by Collins (2018). Significance testing of dichotomous data such as diagnostic status will be conducted with chi-square tests. Sensitivity analysis will be conducted to analyze the impact of dropouts on our results.

We will test mediation of the hypothesized change mechanisms (i.e., knowledge gain of SAD, decrease of dysfunctional social cognitions, decrease of self-focused attention, decrease of avoidance and safety behaviors) of the effect of the treatment components on primary and secondary outcomes (see Fig. 2 above). We will test mediation of the hypothesized change mechanisms by using an approach that allows multiple mediators in one model, as set out by Kraemer et al. (2002).

In addition, we will explore potential moderation of the treatment components by various measured variables (i.e., age, gender, country of origin, nationality, country of parents, mother tongue, relationship status, educational level, employment status, presence of comorbid disorder, use of medication, the severity of SAD). For the analysis of potential moderators, factorial ANOVA and multiple regression analysis will be used.

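### Section 2.8 promises the same power for interactions as for main effects at d = 0.2, which holds only on a halved contrast scale and not on the interaction definition in section 2.1

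*Protocol article*

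**What the plan says.** Section 2.1 (Study design) explains that for a two-way interaction "one has to calculate the difference between the average effect of one component at the two levels of the other component", and then to average over the remaining factors. No division by two is mentioned.

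Section 2.8 (Sample size) states that the study is powered for main and interaction effects. It takes as the smallest clinically relevant difference "Cohen's *d* = 0.2 for the main effect of an individual treatment component or interaction between components on pre-to-post change". The error rates are given as follows: "At an α level of 0.05, a statistical power (1-Beta) of 0.80". For the repeated assessments the section assumes "a correlation between measurements with around 4- and 8-weeks interval of *r* = 0.50". Its conclusion from these inputs is that "we need a total of 384 participants". On attrition, "we conservatively estimate a dropout rate of 20% for our study", which leads to 464 randomized, 29 per condition. The section adds that, because every component has two levels, "the sample size to maintain the power to detect main effects and interactions is the same", and cites a methodological source for this.

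Section 2.9 (Statistical analyses) says "Our primary interest is in testing the main effects and interactions" and codes absence and presence of a component as -1 and +1.

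**The concern.** One number, 0.2, is attached to two quantities without saying that they are measured on different scales. A main effect is a difference between two means, each based on half the sample. The interaction described in section 2.1 is a difference between two such differences, each estimated in half the sample. Its sampling error is larger, so one d cannot carry the same power for both unless the interaction is rescaled.

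This bears on the primary question. Interactions are part of the primary objective, the Introduction motivates the factorial design by possible synergy and antagonism between components, and the Discussion claims enough power for small changes. A reader who takes section 2.1 at its word will believe that the trial has an 80% chance of detecting a 0.2 SD change in one component's effect when another is added. A non-significant interaction could then be taken as evidence that components simply add up, when the trial had little chance of showing otherwise.

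**Working it through.** **Inputs.** From section 2.8: d = 0.2, α = 0.05, target power 0.80, r = 0.50, 384 evaluable, 464 randomized, 20% dropout (464 × 0.8 = 371 evaluable). From section 2.6: equal allocation to 16 conditions. Assumed, because the article does not say: a two-sided test.

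**Scale of the change score.** SD of change = SD × √(2(1 − r)) = SD × √(2 × 0.5) = 1 SD. So d = 0.2 is the same on the raw and the change scale. Baseline adjustment gives residual variance 1 − r² = 0.75, that is, SD 0.866.

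**The plan's own figure.** For a single main-effect contrast on pre-to-post change, N = 4(1.96 + 0.84)²/0.2² ≈ 785, or 786 with equal groups. Baseline-adjusted it is 590. Neither is 384. A repeated-measures calculation with f = 0.1, 16 groups, 4 time points and r = 0.5 does return 384 (power 0.818). That would be a 45-df test of all conditions over all times, (16 − 1) × (4 − 1), not the single contrast described. The software settings are not stated, so this match is an inference.

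**Standard errors.**
- Main effect, N/2 against N/2: variance = 2 × s²/(N/2) = 4s²/N, so SE = 2s/√N.
- Interaction as in section 2.1, four groups of N/4: variance = 4 × s²/(N/4) = 16s²/N, so SE = 4s/√N. Averaging over the other two components pools participants within these four groups and does not halve the contrast.
- Half of that difference: SE = 2s/√N, the same as a main effect. Here 0.2 corresponds to a full difference of 0.4.

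The SE ratio is 2, so the same d needs 2² = 4 times the sample.

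**Effect of the scale alone.** Suppose main effects did have 80% power. The expected z is 1.96 + 0.84 = 2.80. With the SE doubled it is 1.40, and power = Φ(1.40 − 1.96) = Φ(−0.56) ≈ 0.29.

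**Power at the plan's numbers** (effect 0.2, two-sided 0.05):

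| Evaluable N | Analysis | Main effect | Interaction, section 2.1 definition | Interaction, halved scale |
|---|---|---|---|---|
| 384 | change score | 50.0% | 16.5% | 50.0% |
| 384 | baseline-adjusted | 61.9% | 20.5% | 61.9% |
| 371 | change score | 48.7% | 16.1% | 48.7% |
| 371 | baseline-adjusted | 60.4% | 19.9% | 60.4% |

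For example, at 384 on the change score the SE is 4/√384 = 0.204 and z = 0.2/0.204 = 0.98. Power is Φ(0.98 − 1.96) plus a small opposite tail, 0.165. A simulation of the 2 × 2 × 2 × 2 design with 24 per condition gave 50.5%, 16.4% and 49.7% for the three columns of the first row.

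**Detectable difference in effects at 80% power, 371 evaluable.** 2.80 × 4/√371 = 2.80 × 0.208 ≈ 0.58 SD. Baseline-adjusted: 0.58 × 0.866 ≈ 0.50 SD.

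**The case against.** The strongest defence is that the planned analysis uses -1/+1 coding. In a balanced design with that coding, main-effect and interaction coefficients have the same standard error, so equal coefficients have equal power. Halving the interaction changes neither its test nor its p-value. Section 2.8 cites a source for the statement, which is not at hand and may define the interaction on the halved scale, and section 2.1 is a short verbal explanation rather than a declared scale for the power calculation.

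Most of this stands. A reader might infer that the equal-sample-size sentence is simply false, but it is true for effect-coded contrasts. The defence does not settle what d = 0.2 means, however. Section 2.8 calls 0.2 the smallest relevant size for an interaction, and the only interaction definition in the article is unhalved. If the halved scale was meant, the smallest interaction targeted is a 0.4 SD shift in a component's effect, and the article does not say so.

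A reader might also infer that the interaction definition alone pulls power from 80% to 16%, and that it alone creates a need for about 3,140 participants (4 × 785). It does not. The definition accounts for 80% falling to about 29%, and four times the plan's own 384 is 1,536. The rest comes from 384 being too small for a 0.2 main effect on pre-to-post change.

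**Conclusion.** The point holds as an unreconciled scale that makes a stated power figure wrong on the article's own definition. For an interaction of 0.2 as section 2.1 describes it, power is about 29% if main effects have 80%. At 384 evaluable it is about 16% (20% baseline-adjusted), because main-effect power there is about 50% (62% adjusted). These figures assume a two-sided 0.05 test, r = 0.50 and equal allocation. On the halved scale interactions do match main effects, but both then have about 50% power at 384, so this reading does not restore 80% either.

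Two further readings are tempting and are not supported. One is that all 15 effects of a full four-factor model will be tested at an unadjusted 0.05. The article does not say which orders of interaction will be tested and is silent on adjustment, which may be left to an analysis plan. The other is that interactions should become secondary. The objectives place them in the primary question, and moving them would change that objective rather than correct an error.

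**What to change.** 1. State one scale for interactions and use it in both section 2.1 and section 2.8. If it is the halved contrast, say that d = 0.2 then means a 0.4 SD change in a component's effect between levels of the other component. If it is the full difference, drop the claim of equal power.
2. Replace the equal-sample-size sentence with wording such as: *Main effects and interactions have equal power only when the interaction is expressed as half the difference between a component's effects. On the difference-in-effects scale the standard error is twice as large.*
3. Restate the power for interactions, or give the detectable difference in effects at 80% power: about 0.58 SD at 371 evaluable, about 0.50 SD with baseline adjustment. Do this together with a correction of the main-effect calculation behind 384, since the restated figure depends on it.
4. Report each interaction with a confidence interval on the difference-in-effects scale. At 371 evaluable, the 95% half-width on the change score is about 1.96 × 0.208 = 0.41 SD, which shows directly that a non-significant result does not establish additivity.

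The cost is wording and a short recalculation. Randomization, data collection, the model and the tests stay as they are, and interactions keep their place in the primary objective.
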